## Background

Irreversible pulpitis is an inflammatory condition of the dental pulp, highly painful, and one of the main reasons for seeking emergency dental treatment [1, 2]. Pain associated with irreversible pulpitis represents more than 45% of the reasons for dental emergency consultation in hospital [3]. Diagnosis of symptomatic irreversible pulpitis is based on clinical findings such as spontaneous mild to severe pain that remains after removal of the stimulus. The most widely used clinical test is the response to heat or cold sensitivity test. The main etiology of irreversible pulpitis is an infectious lesion due to decay or loss of seal under restorations. After tooth trauma, pulp exposure or cracks can also induce a pulpal inflammatory response [4]. Recommended emergency care is partial endodontic treatment under local and/or locoregional anesthesia [5, 6]. The purpose of emergency partial endodontic treatment is to stop the pain of pulpitis by removing a portion of the pulp [7]. Compared to complete pulpectomy, the pulpotomy procedure results in a lower incidence of post-treatment pain [8, 9]. Several dressings can be used after emergency pulpotomies, camphorated phenol, eugenol, isotonic saline and cresatin, without contribution for the relief of pain [7]. Ideally, complete final endodontic treatment is performed in the following 72 h, as 55% of patients experience moderate to severe pain due to pulpotomy [10, 11]. The dental literature reports major difficulty in achieving adequate anesthesia in the mandible in order to perform partial endodontic treatment, especially for molars [12, 13]. This results in a very painful care experience for the patient [14]. Management of this type of emergency is costly for health facilities in terms of equipment and time as pulpotomy is the only emergency treatment recommended [14]. Patient comfort, cost-saving and rationalization of care time justify the search for an alternative to emergency partial endodontic treatment. A recent systematic review by Shirvani et al. [15] showed superior intraoperative analgesia for patients with irreversible pulpitis after administration of preemptive nonsteroidal anti-inflammatory drugs. But, to our knowledge, no clinical trial on the use of orally administered corticosteroid for the treatment of dental pulp inflammation has been conducted. In current practice, short-course, orally administered corticotherapy (prednisolone) is used to manage oral pain of inflammatory origin [16–18]. Glucocorticoids, thanks to their anti-inflammatory action, can neutralize the inflammatory mediators [19]. Pulp inflammation can be treated using this molecule: the efficacy of intraosseous local steroid injection for irreversible pulpitis of mandibular molars has already been demonstrated, but this results in local comorbidities and requires specific materials [20, 21]. Oral administration of short-course prednisolone is simple and safe but its efficacy to manage pain caused by irreversible pulpitis has not yet been demonstrated. Administration of prednisolone per os has a very high (90%) and rapid (at least 4 h) bioavailability. No difference in efficacy between intravenous and oral administration of this molecule was reported in the case of multiple sclerosis [22]. This oral treatment could limit comorbidities and technical difficulties associated with intraosseous injection and could make it possible for complete endodontic treatment to be delayed to 72 h later in optimal conditions of analgesia for the patient. Despite the difficulties described concerning partial endodontic treatment, it is very effective in terms of pain reduction and can achieve a success rate of 100%. A noninferiority design was, therefore, chosen to compare the effect of short-course, orally administered corticotherapy with partial endodontic treatment in terms of pain reduction during adult emergency care for irreversible pulpitis in permanent mandibular molars.

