### Determination of sample size

Sample size calculation was based on the noninferiority hypothesis that the prescription of short-course corticotherapy would be not less effective than partial endodontic treatment for reducing the pain caused by irreversible pulpitis in mandibular molars.

According to reported results [5], the proportion of patients showing successful relief (presenting pain <5 at 24 h on the NS) in the reference group (partial endodontic treatment) would be 95%. The noninferiority margin was defined as 20% fewer successes in the evaluated group (short-course corticotherapy). The calculation used Newcombe’s formula («lower confidence limit for difference in proportions (simulation)») for the procedure using the 6.0 version of NQuery software and resulted in a sample size of 40 patients per group to achieve 90% power and a one-sided type I error of 0.025.

However, to obtain satisfactory power, two features must be taken into account: (1) a slightly lower proportion of successful treatments in the evaluated group compared to the reference group (power of at least 80% if the treatment group were to have 3% fewer successes or at least 90% if it were to have 2% fewer successes,) and (2) a 5% proportion of patients lost to follow-up or randomly assigned to the corticosteroids group receiving the partial endodontic treatment before the first 24 h due to lack of efficacy [27]. Consequently, it was decided that 60 patients would be enrolled in each group, 120 in total.

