### Statistical analysis

The main analysis will be intention-to-treat (ITT) using the «missing = failure» strategy. A robustness analysis, supported by the per-protocol approach, will be carried out.

The difference between the two arms in the number of patients with pain <5 on the NS will be measured using its unilateral 97.5% confidence interval (CI) according to the binomial exact formula. The noninferiority hypothesis will be accepted if the lower confidence limit is superior to the noninferiority margin, which is fixed as −20%.

For qualitative outcomes, frequencies between the two groups will be compared using the chi-square test, or Yates’s corrected chi-square or Fisher’s exact tests, depending on the variables’ distributions. For quantitative outcomes, means will be compared using Student or Wilcoxon tests according to variables’ distributions. Regression model will be used to adjust on major confounding factors (i.e., age and sex). The statistical significance threshold will be 0.05.

Basic statistics in the study report will include information on missing values for all relevant study variables. A summary of baseline patient characteristics with totals and proportions (%) for categorical variables, and minimum, maximum, interquartile ranges and standard deviations for continuous variables will be presented. An estimation of primary and secondary outcomes will be calculated using their 95% CI.

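### Noninferiority can be declared on the intention-to-treat limit alone: the per-protocol analysis is planned but has no stated effect on the conclusion

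*Protocol article*

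**What the plan says.** Under Statistical analysis, the protocol article ranks the two analyses. The first is primary: "The main analysis will be intention-to-treat (ITT) using the «missing = failure» strategy". The second is supportive: "A robustness analysis, supported by the per-protocol approach, will be carried out". The acceptance rule follows in the singular: "The noninferiority hypothesis will be accepted if the lower confidence limit is superior to the noninferiority margin", which is fixed at −20%. The limit comes from a "unilateral 97.5% confidence interval (CI) according to the binomial exact formula".

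Under Determination of sample size, the reference success rate "in the reference group (partial endodontic treatment) would be 95"%, and "The noninferiority margin was defined as 20% fewer successes in the evaluated group". The calculation gives "a sample size of 40 patients per group to achieve 90% power and a one-sided type I error of 0.025", later raised to 60 per group. The only change of treatment foreseen there is a prednisolone patient who receives the pulpotomy within 24 h.

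Under Protocol violations, membership of the per-protocol set is settled at a blinded review before database lock. That fixes who is in the set, not what its result does to the conclusion.

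**The concern.** In a superiority trial, dilution of the treatment contrast works against the claim, so ITT is the cautious choice. In a noninferiority trial it can work in favor of the claim. If some reference patients do not receive the reference treatment in full and do worse, they stay in the ITT reference arm, lower its success rate and bring the difference closer to zero. A per-protocol analysis is the usual counterweight, but here it carries no weight in the decision: ITT could pass, per-protocol could fail, and noninferiority would still be accepted under the rule as written.

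The Background makes the question worth asking for this reference arm. It reports "major difficulty in achieving adequate anesthesia in the mandible in order to perform partial endodontic treatment", particularly for molars, and mandibular molars are the whole trial population. At stake is whether the one-sided 0.025 protects against accepting a treatment that is 20 points worse than pulpotomy carried out as planned.

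**Working it through.** **Inputs from the protocol article.** Reference success 95%, margin 20 points, one-sided 0.025, 60 per arm, 1:1 allocation. The sample size was computed with Newcombe's lower limit, so that limit is used here. The analysis section names an exact binomial interval without further detail.

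**Formula.** For observed proportions pT (prednisolone) and pC (reference), with lT the lower Wilson limit for prednisolone and uC the upper Wilson limit for the reference (z = 1.96):

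L = (pT − pC) − √[(pT − lT)² + (uC − pC)²]; pass if L > −0.20.

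Pass probabilities with a single rule are exact, summed over all pairs of binomial counts. Joint results come from 400,000 simulated trials.

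**Step 1: the plan's own figures.** At 40 per group and 95% in both arms, power is 92.8%, so the stated 90% is met. At 57 per group (60 × 0.95), power is 93.4% at −2 points and 88.9% at −3 points, so the stated 90% and 80% are met. At 60 per group with a true 75% against 95%, the pass probability is 0.0245, in line with 0.025.

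**Step 2: how a lower reference rate moves the bar.** If 57 of 60 reference patients succeed, prednisolone needs at least 52 of 60 (86.7%). If 54 of 60 succeed, it needs only 50 of 60 (83.3%).

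**Step 3: pass probability when prednisolone is exactly 20 points below completed pulpotomy.** Prednisolone succeeds in 75%, completed pulpotomy in 95%. ASSUMPTION: a share f of reference patients do not complete the pulpotomy and succeed with probability s. The documents give neither figure. The ITT reference rate is 0.95(1 − f) + s·f; for f = 5% and s = 75% this is 0.9025 + 0.0375 = 0.94. In the per-protocol set these patients are excluded.

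| f | s | ITT reference rate | ITT difference (points) | Pass, ITT alone | Pass, both required |
|---|---|---|---|---|---|
| 0 | – | 95.0% | −20.0 | 0.0245 | 0.0245 |
| 5% | 75% | 94.0% | −19.0 | 0.035 | 0.024 |
| 5% | 50% | 92.75% | −17.75 | 0.053 | 0.025 |
| 10% | 75% | 93.0% | −18.0 | 0.049 | 0.025 |
| 10% | 50% | 90.5% | −15.5 | 0.098 | 0.026 |
| 10% | 30% | 88.5% | −13.5 | 0.154 | 0.026 |

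The interval matters. With a continuity-corrected Newcombe limit, the two 5% rows become 0.025 and 0.039.

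**Step 4: power cost of requiring both, exclusions at random.** With 5% of each arm excluded at random from per-protocol, power goes from 0.948 (ITT alone) to 0.934 (both) at −2 points, and from 0.909 to 0.888 at −3 points. Repeat simulations agree to within about 0.004.

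**Step 5: power cost when exclusions are selective.** Suppose 10% of reference patients do not complete, only they are excluded, and prednisolone truly equals the reference strategy as delivered. With s = 50% (both strategies at 90.5%), power falls from 0.939 to 0.817. With s = 30% (both at 88.5%), it falls from 0.908 to 0.673.

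**Step 6: the departure the protocol does foresee.** Suppose 5% of prednisolone patients would fail, receive an early pulpotomy and are credited with 95% success. The ITT pass probability at a true −20 points is 0.114. Requiring both sets, with these patients dropped from per-protocol, still leaves 0.086. Counting them as failures brings it back to 0.024.

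**The case against.** **Disagreement rules belong in the analysis plan, and ITT as primary is conventional.** Choosing ITT is indeed not an error, the acceptance sentence does not name an analysis set, and the blinded review of per-protocol membership is sound. But the article does not leave the decision open: it ranks the analyses and states a single-limit acceptance rule directly beneath. The point is about that stated rule. An unseen analysis plan might add a condition; nothing in the article does.

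**The Background does not say that pulpotomies go uncompleted.** This stands. A reader might infer a substantial non-completion rate from the anesthesia difficulty. The consequence the article draws is a painful experience of care, and it adds that the treatment can nonetheless reach 100% success. No non-completion rate appears anywhere, so the figures in the table are conditional.

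**The pass may not be false.** This also stands in part. A reader might infer that the type I error is simply inflated. If the trial compares strategies as delivered, as the wording of the secondary objective and the practical arguments in the Discussion allow, an uncompleted pulpotomy is a real failure of the reference strategy. A 75% against 90.5% comparison is then a true deficit of 15.5 points, inside the margin. The excess over 0.025 is an error only against pulpotomy as planned.

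**Per-protocol has its own bias.** Removing reference patients with poor outcomes after randomization favors the reference, and Step 5 shows that the power loss can be large. This argues against substituting per-protocol for ITT and against treating exclusion of non-completers as automatic. It does not argue against giving per-protocol a defined role: a joint rule can never pass more often than ITT alone.

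**Conclusion.** The point holds in a limited form. As written, noninferiority rests on the ITT limit alone, and the per-protocol result cannot change the conclusion. For the question of prednisolone against pulpotomy as planned, the pass rate at a true −20 points is then above 0.025 whenever reference patients who do not complete the pulpotomy do worse. On the Newcombe limit it is about 0.035 to 0.053 with 5% not completing at 75% to 50% success, and higher with more. These inputs are assumptions, and a more conservative interval lowers the result.

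The documents do not show that non-completion will be common, that ITT is the wrong primary analysis, or that the stated error rate fails for strategies as delivered. Nor would a both-sets rule settle every adherence problem: it leaves the effect of early pulpotomy in the prednisolone arm largely in place (0.086 in the example), and that needs separate handling. The change is worth making, but the size of the problem is not established.

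**What to change.** Under Statistical analysis, state that noninferiority is concluded only if the lower limit exceeds −20% in both the ITT and the per-protocol analysis, using the same interval method, and that it is not concluded if the two disagree.

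State in advance whether the question is treatment as planned or strategy as delivered, fix accordingly how uncompleted pulpotomies count in the per-protocol set, and report their number by arm. Specify separately how early pulpotomy in the prednisolone arm counts in each analysis, because the both-sets rule does not resolve it.

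The cost is a few sentences, with no added patients. With 5% random exclusions the power loss is about 1.5 to 2 points (0.948 to 0.934 at −2 points, 0.909 to 0.888 at −3 points), still above the stated 90% and 80%. If exclusions fall mainly on reference patients with poor outcomes, the loss can be much larger (0.939 to 0.817, or 0.908 to 0.673, in the Step 5 examples), which is why the per-protocol definition must be decided before the data are seen.

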### Design

A noninferiority, open-label, randomized controlled clinical trial will be conducted in two dental subunits of the Bordeaux University Hospital. Eligible patients will be recruited during their emergency visit when presenting irreversible pulpitis in the first or second mandibular molars. Diagnosis will be based on clinical and radiographic examination. Two parallel groups will be randomized so that patients will receive: (1) partial endodontic treatment (reference) or (2) short-course, orally administered corticotherapy (intervention to evaluate) (Fig. 1).

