#### Outcomes

The primary outcome is the proportion of patients with pain intensity of below 5 on a Numerical Scale (NS <5) 24 h after the emergency visit [25]. The NS has already been used for the assessment of pain in previous studies to evaluate the efficacy of orally administered corticosteroids on pharyngitis presenting as an emergency [26]. Briefly, the patient will be asked to make a pain rating according to a NS score ranging from 0 to 10. A clinical research assistant will directly phone the patient and will use a standardized sentence: «Please indicate the intensity of your pain level on a scale of 0 (no pain) to 10 (worst pain imaginable)».

Secondary outcomes include:Number of analgesic drugs (step 1 on the World Health Organization analgesic ladder (paracetamol 1 g) or step 2 (paracetamol 600 mg/codeine 50 mg) taken after the inclusion visit up to 72 h)Difference in pain measured using the NS between T0 (baseline) and 24 h after the emergency visit (T1)Kinetics of pain, self-assessed using the NS at 6, 12, 24, 48 and 72 h after T0Patient’s comfort during complete endodontic treatment measured using the “Iowa Satisfaction with Anesthesia Scale” (ISAS) [23]Number of injected anesthetic cartridges required to achieve clinical silence for the realization of complete endodontic treatmentNumber of patients returning for the T2 visit

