### Study timelines

All patients seeking emergency consultation at the dental subunits of the Bordeaux University Hospital will be screened for the selection criteria.

If a patient meets all criteria, they will be informed by an investigator of the study, who will tell them about the objectives, methods, follow-up, risks and restrictions. They will be given an Information Sheet and an Informed Consent Form so that they can read them and ask any questions. If the patient agrees, they will sign the Informed Consent Form and will be included in the study (T0).

The investigator in charge of the emergency room will proceed to randomization (see below) and another investigator will conduct the T0 (baseline) visit according to the affected group to which the patient will be allocated. The patient will be contacted directly by a research assistant, blinded to the affected group, 24 h after inclusion to gather the information on pain intensity 24 h after the emergency visit (T1). The patient will then receive complete endodontic treatment 72 h after T0 (T2) (Fig. 2).

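### Baseline pain (T0 NS) is collected but is not a covariate for the secondary pain outcomes: the raw change comparison is valid but less precise than ANCOVA, and the timing of the T0 rating relative to randomization needs stating

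*Protocol article*

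**What the plan says.** The Outcomes section lists as a secondary outcome "Difference in pain measured using the NS between T0 (baseline) and 24 h after the emergency visit". A T0 pain score is therefore collected on every patient, on the same 0 to 10 scale as the 24 h score. Pain at 6, 12, 24, 48 and 72 h is a further secondary outcome.

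The Statistical analysis section gives one general rule: "For quantitative outcomes, means will be compared using Student or Wilcoxon tests according to variables’ distributions". On adjustment it says "Regression model will be used to adjust on major confounding factors (i.e., age and sex"). The abbreviation closes the list at two variables. The section does not say which outcomes the model serves. Neither it nor the Randomization section names T0 pain as a covariate or stratification factor.

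On timing, the Study timelines section uses T0 twice. Before randomization, patients who agree to take part: "they will sign the Informed Consent Form and will be included in the study (T0"). After randomization: "another investigator will conduct the T0 (baseline) visit according to the affected group to which the patient will be allocated". The Design section states that the trial is open-label. The schedule of assessments (Fig. 2) is not reproduced in the text available.

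**The concern.** In a randomized trial, covariates are adjusted for to gain precision and to guard against chance imbalance. Randomization already removes systematic confounding, which is the reason the article gives for choosing age and sex. The pre-treatment value of the outcome itself is the natural first covariate, and here it costs nothing.

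Subtracting the baseline is not the same as adjusting for it. Subtraction assumes a slope of 1 of 24 h pain on T0 pain. When the true slope is lower, the change score over-corrects: it adds the noise of the T0 score and passes on part of any chance T0 difference between the arms.

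What is at stake is the width of the confidence intervals that the article promises for the secondary outcomes. The pain-change result will be read as support for, or against, the binary primary result, and an avoidably wide interval weakens it in that role. The two uses of T0 raise a separate question: whether the baseline score is sure to be free of knowledge of the arm.

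**Working it through.** **Inputs.** 60 patients per arm, 1:1 (Determination of sample size; Randomization). The article gives no variance, correlation or target difference for NS pain, so there is no planned precision figure to reproduce for this outcome. The 60 itself is consistent with the article's conditions. Newcombe's limit with continuity correction needs 56 per arm for at least 90% power at 2% fewer successes, and 56/0.95 = 58.9, rounded up to 59. Assumed: correlation r between T0 and 24 h NS of 0.2 to 0.5, and the same SD s at both times.

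**Step 1: variance per patient.**
- Change score: 2(1 − r)s²
- 24 h score alone: s²
- ANCOVA (24 h NS on arm and T0 NS): (1 − r²)s²
- Ratio ANCOVA/change: (1 − r²)/[2(1 − r)] = (1 + r)/2
- Ratio ANCOVA/24 h score: 1 − r²

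| r | Change | ANCOVA | ANCOVA/change | ANCOVA/24 h score |
|---|---|---|---|---|
| 0.2 | 1.60 s² | 0.96 s² | 0.60 | 0.96 |
| 0.4 | 1.20 s² | 0.84 s² | 0.70 | 0.84 |
| 0.5 | 1.00 s² | 0.75 s² | 0.75 | 0.75 |

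Against the change score, the gain equals 1/0.60 = 1.67 to 1/0.75 = 1.33 times the patients for that outcome. Against the raw 24 h score it is 1/0.96 = 1.04 to 1/0.75 = 1.33 times. Confidence intervals shrink to √0.60 = 0.77 to √0.75 = 0.87 of the width for the change score. Below r = 0.5 the change score is less precise than ignoring T0 altogether. At r = 0.7 the ANCOVA/change ratio is still 0.85.

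**Step 2: power, for illustration.** Assume a true difference of 0.5 s and a two-sided 0.05 test. Power = Φ(0.5/√V × √(60/2) − 1.96), where V is the variance above in units of s².

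| r | Change | 24 h score | ANCOVA |
|---|---|---|---|
| 0.2 | 58.1% | 78.2% | 79.8% |
| 0.4 | 70.5% | 78.2% | 84.8% |
| 0.5 | 78.2% | 78.2% | 88.5% |

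**Step 3: chance imbalance.** If the arms differ by D in mean T0 pain, the expected 24 h difference moves by rD, so the change comparison moves by rD − D = −(1 − r)D. The standard error of D is s√(2/60) = 0.183 s. A one-standard-error imbalance therefore moves the change result by 0.8 × 0.183 = 0.15 s at r = 0.2, or 0.5 × 0.183 = 0.09 s at r = 0.5. ANCOVA removes this shift.

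**Step 4: what a baseline rated after allocation would do.** Suppose knowledge of the arm shifted one arm's T0 score by 1 point (assumed). In simulation (60 per arm, SD 2, no true effect, 4,000 runs) the average error was as follows, in points:

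| r | Change | ANCOVA | 24 h score |
|---|---|---|---|
| 0.2 | 1.01 | 0.21 | 0.01 |
| 0.4 | 1.01 | 0.40 | 0.00 |
| 0.6 | 1.00 | 0.60 | 0.01 |

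The change score takes the whole shift, and ANCOVA about r times it. ANCOVA therefore does not repair a contaminated baseline; rating before randomization does.

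**The case against.** **The plan is not in error.** A Student or Wilcoxon test on change is valid under 1:1 randomization, and leaving out a prognostic covariate costs efficiency without biasing the comparison. This stands. The point is an inexpensive improvement to a stated choice.

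**The size depends on assumptions and on the comparator.** This also stands. The largest gain over the change score occurs at r = 0.2, where T0 explains only 0.2² = 4% of 24 h variance and the gain over the plain 24 h score is about 4%. The documents do not support calling T0 pain the strongest predictor. Equal spread is doubtful too, since the article expects 95% of the reference arm below 5 at 24 h. That affects the ratio but not its direction: if the 24 h SD is k times the T0 SD, change variance minus ANCOVA variance is (1 − rk)² times the T0 variance, which is never negative. The ratios apply to comparisons of means; no figure was worked out for the Wilcoxon alternative.

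**A reader might infer that baseline pain is rated after open allocation, so the change score is biased.** The text does not support this. No sentence gives the moment of the T0 rating. T0 is attached to consent before randomization as well as to the later visit, whose description also fits simple delivery of the allocated care. The figure that might settle the order is not shown. The NS is the patient's own rating, and nothing says that patients learn their arm before giving it. What remains is an ambiguity with a possible bias.

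**A reader might infer that the five kinetics time points will each get a separate two-sample test.** The article gives only its general rule for quantitative outcomes and does not describe the kinetics analysis, which may properly be left to the analysis plan.

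**Conclusion.** The point holds for the secondary pain outcomes and is of moderate weight. For the T0-24 h change, the article prescribes an unadjusted comparison and limits the named adjusters to age and sex, although T0 pain is available. With equal variances and r assumed at 0.2 to 0.5, ANCOVA has 0.60 to 0.75 of the variance of the raw change, and 0.96 to 0.75 of that of the raw 24 h score. It also removes the effect of chance T0 imbalance.

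The double use of T0 calls for a clarifying sentence. A rating after allocation could bias the change score, but the text does not show that this will happen.

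It would be wrong to carry the point over to the main conclusion. The primary outcome is the proportion with NS below 5 at 24 h, judged by a confidence limit on a difference in proportions. It uses no T0 score, and neither its validity nor its planned size is in question here.

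**What to change.** 1. Analyse 24 h NS by ANCOVA on arm and T0 NS, and report the adjusted mean difference with its 95% CI. The raw change can still be described.
2. Add T0 NS to the prespecified covariates for the secondary pain analyses, with or without age and sex, and describe the purpose as precision and protection against chance imbalance instead of confounding. Use the same covariate in whatever model is applied to the 6 to 72 h kinetics.
3. State in Study timelines that the T0 NS is rated and recorded after consent and before the randomization website is opened. Use separate labels for inclusion and for the visit at which the allocated care is given.

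The cost is a few sentences in the protocol and analysis plan and a fixed order of two steps at the emergency visit. No new data, visits or patients are needed.
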